# Effect of acupuncture on cerebrovascular reserve in patients with acute cerebral infarction: protocol for a randomized controlled pilot study

**DOI:** 10.1186/s13063-017-2013-5

**Published:** 2017-06-24

**Keywords:** Stroke, Cerebrovascular reserve, Acupuncture, Acute cerebral infarction, Acupoints

## Abstract

**Background:**

The incidence of cerebral infarction has been growing year by year in China and around the world. According to clinical observation, acupuncture utilizing the “waking up the spirit” needling method is widely used in patients with cerebral infarction, though the underlying mechanisms remain unclear. Additionally, a number of studies have begun to focus on the relationship between cerebrovascular reserve (CVR) and cerebral infarction. The present study aims to investigate whether CVR is one of potential mechanisms underpinning this effect of acupuncture on patients with cerebral infarction.

**Methods:**

This is a single-centre, prospective, single-blinded, randomized controlled pilot study. Sixty eligible patients will be randomized into an intervention group (waking up the spirit acupuncture) and a control group (hand and foot 12-meridian acupuncture) in a 1:1 ratio. All treatments will be conducted once a day on weekdays followed by a 2-day rest period on the weekend, over a total treatment course of 2 weeks. The primary outcome measures are cerebrovascular reserve (CVR) capacity and Breath-holding Index (BHI) which will be evaluated at baseline and 2 weeks after the first acupuncture treatment, and the secondary outcome measures are National Institutes of Health Stroke Scale (NIHSS) and Barthel Index scores which will be used to further evaluate the efficacy of the intervention.

**Discussion:**

Cerebrovascular reserve is an independent risk factor for the occurrence, progression, and recurrence of cerebral infarction that requires attention. This trial aims to investigate whether acupuncture utilizing the waking up the spirit needling method can improve CVR capacity in patients with acute cerebral infarction, thus reducing NIHSS scores and preventing further progression of the disease. Furthermore, data and evidence gained from this study will be utilized in the development of future research projects regarding the effects of acupuncture in patients with acute cerebral infarction.

**Trial registration:**

ISRCTN, ID: ISRCTN99117074. Registered on 20 April 2016.

**Electronic supplementary material:**

The online version of this article (doi:10.1186/s13063-017-2013-5) contains supplementary material, which is available to authorized users.

## Background

Acute cerebral infarction is a relatively common condition whose incidence is increasing around the world, with high rates of morbidity, mortality, and disability [1–6]. Increasingly stressful social conditions and unhealthy lifestyles contribute to the increased incidence of cerebral infarction in younger individuals [7–10], negatively impacting both families and society at large [2, 3, 11]. The incidence of cerebral infarction in China is nearly the highest in the world, and cerebrovascular disease has ranked among the leading causes of death in China since 2008 [2, 12, 13] and has become the third leading cause of death, behind malignant neoplasms and heart disease, according to a 2014 fact sheet published by the Chinese CDC [14]. Systematic analyses have estimated that about 1.7 billion Chinese patients die of cerebral infarction every year, with a recurrence rate greater than 17.1% [11] in surviving individuals.

Cerebral infarction is closely related to cerebrovascular stenosis or cerebral thrombosis. Deficiencies in cerebral perfusion are associated with three compensatory mechanisms of the cerebrovasculature: establishment of collateral circulation, cerebrovascular reserve (CVR), and metabolic reserve. CVR—also known as cerebral blood flow reserve, cerebral perfusion reserve, and cerebral circulation reserve—refers to the ability of the cerebrovasculature to maintain normal cerebral blood flow under physiological or pathological stimulation by via compensatory adjustment of small arteries and capillaries [15]. In the early stages of cerebral ischemia, collateral circulation is established, and blood flow velocity is increased in order to maintain cerebral perfusion volume. When the collateral circulation can no longer compensate for the deficiency in perfusion, CVR begins to increase perfusion by dilating small cerebral arteries and capillaries. When CVR can no longer support further increases in cerebral perfusion volume, brain tissue can only maintain the intracranial blood supply by increasing oxygen fraction extraction. However, as the degree of cerebral anoxia worsens, acute infarction becomes more likely to occur [16]. Patients with low CVR tend to experience more severe hypoperfusion, ischemia, and hypoxia, leading to infarction and further tissue damage [17]. Deficient CVR is not only an independent risk factor for cerebral infarction [18–21] but also a risk factor for the progression [22–25] and recurrence [26] of cerebral infarction. Therefore, the development of novel strategies for increasing CVR in patients with acute infarction is crucial for preventing the progression and recurrence of infarction.

The treatment of acute ischemic cerebral infarction aims to maintain the blood supply and oxygenation of the ischemic penumbra. CVR is closely connected with cerebrovascular diseases and research on cerebrovascular disease has become increasingly focused on CVR [27–32]. Research has also indicated that acupuncture exerts specific effects on blood flow velocity, vascular reactivity, and circulation [33–36], suggesting that acupuncture may improve outcomes in patients with diminished CVR. To the best of our knowledge, however, reports have yet to demonstrate the effect of acupuncture on CVR. Therefore, the present study aims to investigate whether acupuncture utilizing [37] the “waking up the spirit” needling method can improve CVR capacity in patients with acute cerebral infarction. Different methods of acupuncture have varying influences on blood flow, and stronger stimulation may be required to improve blood flow in patients with cerebral infarction [38–41]. Acupuncture utilizing the waking up the spirit needling method provides intense stimulation of the head and limbs by means of bloodletting at certain acupoints, and the positive effects of acupuncture in general have been documented with regard to a number of conditions, including increased cerebral blood flow in the region surrounding the ischemic area [42–44]. Butylphthalide [45] has an effect on patients with acute cerebral infarction; the underlying mechanism maybe that it changes CVR by changing blood flow. As with butylphthalide, we are trying to explore whether acupuncture, utilizing the waking up the spirit needling method, has the same routine mechanism that can improve CVR in patients with acute cerebral infarction, thus reducing scores on the National Institutes of Health Stroke Scale (NIHSS) and preventing further disease progression.

Though a variety of methods may be used to assess CVR (positron emission tomography (PET), single photon emission computed tomography, computed tomography (CT) angiography, magnetic resonance (MR) angiography, transcranial Doppler (TCD) sonography, etc. [46], PET is the most effective in evaluating the capacity for vascular dilatation. However, this method is expensive and relatively underutilized in China. TCD, on the other hand, allows for the noninvasive examination of local blood flow velocity in the middle cerebral artery [47]. Blood flow is proportional to blood flow velocity [48], allowing for the indirect evaluation of CVR using TCD. TCD has been utilized in clinical examination for nearly 30 years and is easy to perform, noninvasive, inexpensive, and repeatable [47]. Some studies have also reported that TCD is effective in evaluating cerebrovascular reactivity using the breath-holding test. [49–51]. For these reasons, we chose TCD to assess CVR in the present study.

## Methods

### Objectives

The present study aims to test the hypothesis that acupuncture utilizing the waking up the spirit needling method can improve CVR capacity in patients with acute cerebral infarction, thus reducing NIHSS scores and preventing further disease progression.

### Recruitment

The present study is a single-center, prospective single-blinded, randomized controlled pilot trial to be carried out in three stages (Fig. 1): a recruitment period prior to baseline assessment and randomization, a treatment and observation period of 2 weeks, and a final follow-up period. All participants will be recruited from the three acupuncture wards of Beijing Hospital of Traditional Chinese Medicine at Capital Medical University (Beijing, China). In the first stage, we will seek out potentially qualified patients according to the inclusion and exclusion criteria and provide them with detailed information about the study such as the research objective, study procedure, and both the potential benefits and risks. If a patient agrees to participate, they will be asked to voluntarily provide written informed consent, following which baseline assessments and randomization will be conducted. Table 1 depicts the timetable of the trial. Figure 2 illustrates the Standard Protocol Items: Recommendations for Interventional Trials (SPIRIT) Figure which the trial protocol follows (Additional file 1).

**Fig. 1 Fig1:**
[figure not shown]
Flow chart

**Table 1 Tab1:** Time table

	Baseline (before treatment)	Treatment			Follow-up and data collection
		Week 0	Week 1	Week 2	Data collection and analysis
Patients entered					
Medical history	√				
GCS	√				
CVR	√				
Sign the informed consent	√				
Randomization	√				
Intervention		√	√	√	
Outcomes					
Primary outcomes					
CVR		√		√	
BHI		√		√	
Secondary outcome					
NIHSS		√	√	√	
Barthel Index		√	√	√	
Adverse events	√	√	√	√	√
Data collection					√

*GCS* Glasgow Coma Scale, *CVR* cerebrovascular reserve, *BHI* Breath-holding Index, *NIHSS* National Institutes of Health Stroke Scale

**Fig. 2 Fig2:**
[figure not shown]
Standard Protocol Items: Recommendations for Interventional Trials (SPIRIT) Figure

### Design

#### Randomization and allocation concealment

The randomization scheme was provided by a random number table. A set of 60 random numbers was generated by a designated computer, and each number was then divided by 2. Resulting numbers with a remainder of 0 corresponded to the treatment group, while those with a remainder of 1 corresponded to the control group. However, this system resulted in 36 control numbers and only 24 treatment numbers, so it was necessary to re-assign six numbers from the control group to the treatment group. The next six numbers were chosen from the random number table and divided by 36, resulting in the following remainders: 26, 24, 6, 2, 22, and 14. Therefore, we assigned patient numbers 26, 24, 6, 2, 22, and 14 into the treatment group, resulting in a total of 30 patients in each group. Participants will be allocated into one of these two groups according to the order in which they are recruited.

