### Trial status

At the time of manuscript submission, we started to seek out potentially appropriate patients from the three acupuncture wards of Beijing Hospital of Traditional Chinese Medicine Affiliated to Capital Medical University according to the inclusion and exclusion criteria and provided them with detailed information about the study. About six patient agreed to participate, after which followed written informed consent and baseline assessments and randomization. We also tried to do some test work before the real recruitment started. However, by the time of manuscript submission we had not started to apply the interventions.

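### The re-balancing step divides by the number of controls but uses the remainders as patient numbers; read literally, it discloses up to six allocations and does not ensure 30:30

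*Protocol article*

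**What the plan says.** All but the last of these statements come from the protocol article, Design, Randomization and allocation concealment.

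- The list: "A set of 60 random numbers was generated by a designated computer, and each number was then divided by 2". Even numbers went to treatment and odd numbers to control.
- The result: "this system resulted in 36 control numbers and only 24 treatment numbers".
- The stated need: "it was necessary to re-assign six numbers from the control group to the treatment group".
- The selection of the six: further numbers were taken from the random number table and "divided by 36, resulting in the following remainders: 26, 24, 6, 2, 22, and 14".
- Their use: "Therefore, we assigned patient numbers 26, 24, 6, 2, 22, and 14 into the treatment group, resulting in a total of 30 patients".
- How the list is applied: "Participants will be allocated into one of these two groups according to the order in which they are recruited".
- Recruitment at manuscript submission (Trial status): "About six patient agreed to participate, after which followed written informed consent and baseline assessments and randomization". The same section says that no intervention had yet been applied.

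The Sample size section also gives 30 per group. The section heading names allocation concealment, but the text under it describes no concealment step.

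**The concern.** Dividing by 36 makes sense only if each remainder points to a place among the 36 control numbers. The article instead treats the remainders as numbers of patients out of 60. These are different operations, and they switch different patients.

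Two things are at stake. The first is whether the list is what the article says it is: balanced 30:30, with the same treatment probability throughout. The second is foreseeability. With allocation in order of recruitment, a recruiter who knows that a given enrolment number is a treatment slot can bring a patient forward or hold one back. This is practical here: recruitment is from three wards of one hospital, onset may be any time under 7 days, and therapists know the treatments. The blinding described for data managers and statisticians does not extend to recruiting staff. The planned between-group comparisons are t tests and chi-square tests, and no analysis reliably removes selection bias introduced at enrolment.

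**Working it through.** **Inputs** (Randomization and allocation concealment; Trial status): 60 numbers; 36 control and 24 treatment before correction; six remainders on division by 36, namely 26, 24, 6, 2, 22 and 14, all distinct; about six patients randomised at submission.

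**Reproducing the stated 30:30 (remainders as positions among the 36 controls).** Six distinct positions pick six distinct controls.
- Treatment: 24 + 6 = 30. Control: 36 − 6 = 30. The stated figure reproduces.
- Treatment probability at any place on the list: 24/60 + (36/60) × (6/36) = 0.40 + 0.10 = 0.50. A simulation of 50,000 lists gave 0.50 for places 1–36 and 0.50 for places 37–60.
- The printed numbers do not identify patients. The kth control has k − 1 controls and up to 24 treatment numbers before it, so it lies anywhere from place k to place k + 24. Position 26, for example, is somewhere from patient 26 to patient 50.

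**Remainders taken literally as patient numbers.** Assume that the odd/even assignment is independent of the six later draws. The count of controls among the six is then hypergeometric (60 numbers, 36 controls, 6 drawn).
- P(all six were controls, giving 30:30) = C(36,6)/C(60,6) = 1,947,792/50,063,860 = 0.039.
- Expected controls among the six: 6 × 36/60 = 3.6. Expected split: 24 + 3.6 = 27.6 treatment and 36 − 3.6 = 32.4 control.
- Most likely split: 28:32, probability 0.325.
- Remainders on division by 36 run from 0 to 35. If 0 is taken to mean 36, patients 1–36 can be switched and patients 37–60 cannot.
- Treatment probability, patients 1–36: 0.40 + 0.60 × 6/36 = 0.50. Patients 37–60: 24/60 = 0.40. The simulation gave 0.50 and 0.40.
- Check: (36 × 0.50 + 24 × 0.40)/60 = 27.6/60, which agrees with the expected split.

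**Disclosure on the literal reading.**
- Allocations identified: 6/60 = 10% of the list, or 6/30 = 20% of the treatment arm.
- With about six patients randomised at submission, numbers 2 and 6 may already have been used. Numbers 14, 22, 24 and 26 had not.
- If the list is 30:30, the other 54 places hold 30 − 6 = 24 treatment and 30 control, so an unlisted number is control with probability 30/54 = 55.6%.

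**The case against.** The strongest reply is that the position reading is the natural one. The text says the six were to come from the control group, the divisor equals the count of controls, and the article reports that 30 per group resulted. On that reading the draw is a proper random selection, the probability is 0.50 throughout, and no patient is directly identified. This stands. The 3.9% is a property of the literal method. It is not evidence that the actual list failed to balance, and it may equally suggest that the literal reading is not what was done.

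Four stronger conclusions are therefore not supported:
- **That 30:30 is wrong.** It follows exactly on one reading, and on the other it is possible but not assured.
- **That the six were picked by hand or by judgement.** They came from further random numbers.
- **That the list was open or the whole allocation unconcealed.** The article does not say who held the list. Allocation in order of recruitment describes any sequential scheme, and a condensed article may leave the concealment procedure to the full protocol. At most 6 of 60 assignments are shown to be disclosed.
- **That future allocations were still exposed when the article appeared on 24 June 2017.** Enrolment is given only at submission, and the submission date is not given.

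A reader might also set the first 26 patients, (6 + 20 × 24/54)/26 = 57%, against 24/54 = 44% in the rest. That assumes all six were controls and cuts the list at the largest number drawn. Cutting at 35, the largest possible remainder, gives (6 + 29 × 24/54)/35 = 54% against 44%. I do not rely on either contrast.

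The reply does not rescue the text. Under the position reading, the sentence naming patient numbers is wrong. Under the literal reading, an unseen concealment procedure could not hide numbers that the article itself prints.

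**Conclusion.** The point holds as a fault of the procedure as written, with consequences that depend on what was done.

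- **If the remainders are patient numbers:** up to 10% of allocations are disclosed, including four future ones as of submission. The method does not ensure 30:30 (3.9% chance; expected 27.6:32.4). Treatment probability falls from 0.50 to 0.40 for patients 37–60.
- **If they are positions among the controls:** the list is sound and 30:30, but the article misdescribes which patients were switched. Had someone edited the list from that description, the wrong patients would have been moved.

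Disclosure and a failed split are not established together. The disclosure requires the literal reading, and even then the six may all have been controls. The probabilities assume independent draws, and the boundary at 36 assumes that a remainder of 0 means 36. The documents cannot settle which reading applies; the actual list can.

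**What to change.** 1. Establish from the working record whether the remainders were used as patient numbers or as positions among the 36 controls, and check the actual list against 30:30.
2. Correct the description so that it matches what was done.
3. Keep every allocation already made.
4. Have a person independent of recruitment, treatment and the analysis regenerate the unused remainder by computer, in blocks of randomly varying size. The totals should bring each arm to 30, so the treatment places left equal 30 minus those already allocated to treatment.
5. That person should hold the list. A non-analysing member of the statistics centre would serve. The analysing statisticians should not hold it, because the Statistical analysis section keeps them blinded to the entire allocation process.
6. Release each assignment only after consent, eligibility and baseline assessment are recorded, and say so in the protocol.

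The cost is a few hours of work and a short amendment. At submission no intervention had been applied and about 54 of the 60 places (60 − 6) were unused. If recruitment has since moved on, the same steps apply to whatever part of the list is left. The printed numbers need not be withdrawn, because regenerating the unused part makes them uninformative.

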#### Blinding

The therapists will be aware of the treatments in both groups as they are experienced enough to distinguish between the treatment methods; however, the participants will remain blinded to the treatment. Participants will be told that they have been randomly allocated to either the treatment group or the control group, and they will be treated with bloodletting using a three-edged needle, regular acupuncture, or both, based upon their condition. Moreover, the study will utilize independent data managers and statisticians who will also remained blinded to the intervention methods throughout the trial. All therapists, data managers, and statisticians have been requested to refrain from communication with each other regarding the study.

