### Data management

All researchers including therapists, data entry clerks, the data collector, data manager, statistician, and outcome assessors will receive special training regarding the research contents and data management. During the recruitment period, our data collector will record the baseline characteristics of participants on CRFs, and all data will be assessed by the data manager. Then, as the study begins, the data collector will obtain CVR, BHI, NIHSS, and Barthel Index data at baseline and 2 weeks following the first treatment. Additional NIHSS and Barthel Index data will be obtained 1 week following the first treatment. The TCD assessment will be conducted by an appointed operator who has completed an advanced course of study in this field at Beijing Tiantan Hospital Affiliated with Capital Medical University.

Upon conclusion of the treatment period, all participant data will be completed and recorded on the original CRFs. The data will then be entered into Excel spreadsheets by two separate data entry clerks, following which the data manager will compare the accuracy of the two datasets. If any differences are noted, corrections will be made according to, and marked on, the original CRFs. The data will be managed in accordance with the Data Protection Act of 1998 [58]. All paper files related to the research will be saved in a locked filing cabinet, while electronic documents will be stored in a special computer which will remain password-protected and accessible only to the principal investigators. All research documents, including both the paper files and electronic documents, will be preserved for at least 5 years after publication. If readers have any questions regarding our published data, they will be permitted to contact our first author or corresponding author to ask for the original data.

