### Ethical considerations

The trial protocol is in accordance with the principles of the Declaration of Helsinki [59] and was approved by the Research Ethical Committee of Beijing Hospital of Traditional Chinese Medicine at Capital Medical University on 30 November 2015 (Ethics Reference Number: 20151130). This trial was registered at ISRCTN (ID: 99117074). Each participant will be notified regarding the study protocol. Written informed consent will be obtained from every participant.

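### Participants are called blinded although only one arm is bled, they are told that their condition decides the procedure, and masking of the people who measure the outcomes is not stated

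*Protocol article*

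**What the plan says.** The Abstract of the protocol article describes a "single-centre, prospective, single-blinded, randomized controlled pilot study", and Recruitment repeats the single-blinded label. The Blinding section then gives the status of each role it covers:

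- Therapists: "The therapists will be aware of the treatments in both groups".
- Participants: "the participants will remain blinded to the treatment".
- Data managers and statisticians: "the study will utilize independent data managers and statisticians who will also remained blinded to the intervention methods throughout the trial".
- Communication: "All therapists, data managers, and statisticians have been requested to refrain from communication with each other regarding the study".

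The same section says what participants hear. They learn that they were randomized to the treatment or the control group, and also that "they will be treated with bloodletting using a three-edged needle, regular acupuncture, or both, based upon their condition".

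The people who generate the outcome data appear only under Data management. There, "The TCD assessment will be conducted by an appointed operator", whose advanced training is described, and outcome assessors and a data collector are listed among the staff to be trained. Neither that section nor any other says whether these people know the arm. Statistical analysis repeats only that the statisticians are blinded.

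**The concern.** Three things in the Blinding section do not fit the rest of the article.

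First, blinding to treatment is claimed for patients who can tell whether they are being bled.

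Second, the script gives patients two explanations of why they receive a given procedure, chance and their condition. Under the design, only the first is true.

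Third, the protection is placed downstream of the measurements. Data managers and statisticians handle numbers that already exist. The operator who records the flow velocities and the assessors who score NIHSS and Barthel create those numbers, and they are not listed.

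At stake are both primary outcomes and both secondary outcomes. CVR and BHI need the patient's cooperation in a breath-hold and an operator's recording; NIHSS and Barthel are rated scales. If expectation or knowledge of the arm shifts any of these, no later analysis step removes it. The Sample size section also intends the pilot's results to feed the calculation for later trials, so a biased difference would carry forward.

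**Working it through.** The plan gives no figure on this point to reproduce, so the check is mainly a comparison of sections.

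**1. Can participants be blind to the procedure?**
- Treatment group section: a three-edged needle is inserted about 5–10 mm at *Bai Hui*, *Si Shen Cong* and 12 well-points, the skin is squeezed until it bleeds, and filiform needles follow.
- Control group section: filiform needles only.
- Intervention section: once a day on weekdays for 2 weeks, nominally 5 × 2 = 10 sessions.
- Inclusion criteria: Glasgow Coma Scale score of at least 12.
- Blinding section: patients hear beforehand that bloodletting and regular acupuncture are the possibilities.

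A patient who has been told of both possibilities will recognize which one is used. What can stay hidden is which of the two is the method under test.

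**2. Does condition decide the procedure?**
- Randomization and allocation concealment: a pre-generated list, applied in order of recruitment, decides the group.
- Treatment group and Control group sections: the group decides the procedure. Neither makes bloodletting depend on the patient's condition.
- Participant script: condition decides.

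The script contradicts both the design and its own statement about random allocation.

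**3. Which roles are covered?**
- Blinding stated: participants, data managers, statisticians.
- Awareness stated: therapists.
- No-communication rule: therapists, data managers, statisticians.
- In neither list: TCD operator, outcome assessors, data collector.

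As written, nothing restricts therapists from discussing a patient's arm with the operator or the assessors.

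**4. Do the primary outcomes leave room for influence?**
The primary outcome section sets a breath-hold of at least 15 s with no upper limit, and defines CVR as the percentage rise in velocity and BHI as that percentage divided by hold time. Take a 20% rise, the article's impairment threshold:
- 15 s: 20 / 15 = 1.33
- 20 s: 20 / 20 = 1.00
- 30 s: 20 / 30 = 0.67

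If the rise is fixed, a longer hold lowers BHI and leaves CVR unchanged. If instead the rise were proportional to hold time, a longer hold would raise CVR and leave BHI unchanged. The article states neither relation. Hold time therefore matters, but the direction of its effect cannot be derived.

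**5. How sensitive is a comparison of this size? (assumption only)**
Inputs from the article: 30 per arm (Sample size); independent-samples *t* test, two-sided, 0.05 (Statistical analysis). Assumed: no true effect, all 60 analysed, and a constant shift of *b* SD between arms. The article gives no SD and no bias.

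Degrees of freedom = 2 × 30 − 2 = 58. Noncentrality = *b* × √(30/2) = 3.873 *b*. The probability of P < 0.05 from the noncentral *t* distribution is:
- *b* = 0: 5.0%
- *b* = 0.1 (noncentrality 0.39): 6.7%
- *b* = 0.2 (0.77): 11.9%
- *b* = 0.3 (1.16): 20.8%
- *b* = 0.5 (1.94): 47.8%

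**The case against.** The best reply is that this is a condensed article, that the full protocol is not shown, and that a specially appointed TCD operator and assessors listed apart from the therapists fit well with independent, masked measurement. Part of that stands. The article is silent; it does not declare these people unblinded, and a reader who infers that they know the arm goes beyond the text. Condensation does not dispose of the point, however. The article has a dedicated Blinding section that goes through roles and sets a communication rule, and the roles that produce the outcomes are absent from both.

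A second reply is that both arms receive genuine acupuncture in common clinical use (Discussion) and that the script does not identify the experimental method. This also stands: it would be too strong to say that no form of participant masking is possible. What fails is the claim that patients are blind to the treatment itself.

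Third, a reader might infer from "Each participant will be notified regarding the study protocol" under Ethical considerations that the procedure of each arm is spelled out at consent. That sentence, and the mention of study procedure under Recruitment, do not say so. The argument needs only the script in the Blinding section.

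Fourth, the remark about condition might be taken to mean that allocation itself was adapted to the patient. The randomization section does not support that. The remark belongs to what patients are told, and the same sentence also tells them that allocation was random.

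**Conclusion.** The point holds as a fault in stated wording and in coverage. The claim of participant blinding does not match the procedures described, the participant script contradicts random allocation to fixed procedures, and the Blinding section leaves out the operator and the assessors. Measurement of all four outcomes is therefore not shown to be protected, and the single-blinded label currently rests on its weakest part.

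The document does not show that bias will occur, which arm it would favour, or how large it would be. The range of about 7% to 48% rests wholly on an assumed shift of 0.1 to 0.5 SD and shows only how sensitive a comparison of 30 against 30 is; no single value in it deserves weight. Nor can a fixed gain in CVR per extra second of breath-holding be asserted, because that needs a relation between velocity and hold time that the article does not give.

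**What to change.** 1. Specify in the Blinding section that the already appointed TCD operator and the NIHSS and Barthel assessors are masked to arm and are not treating therapists, and add them to the no-communication rule.
2. Replace the statement that "the participants will remain blinded to the treatment" with one that participants are not told which method is under test. Base any single-blinded label on assessor masking, once that is in place.
3. In the participant information, delete the closing phrase that makes the procedure depend on condition, or otherwise reconcile it with random allocation and the arm-specific procedures.

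The cost is small. The assessor roles already exist, and Trial status says that no intervention had been applied at submission. The changes are mostly wording, with minor scheduling to keep assessors apart from treatment. If the roughly six patients who had already agreed were given the present script, they would need the corrected one. The trial would also give up its claim to full participant blinding.
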